**Figure 1 F1:**
[figure not shown]
Study flow diagram.

This paper describes the study protocol (Dated September 30, 2019; Protocol Version 1.0) to comply with the Standard Protocol Items: Recommendations for Interventional Trials (SPIRIT) (Chan et al., 2013), see Supplementary Table 1 for Spirit Checklist. The trial will be conducted according to the Consolidated Standards of Reporting Trials (CONSORT) of Electronic and Mobile HEalth Applications and onLine TeleHealth (CONSORT E-HEALTH) statement (Eysenbach, 2011), CONSORT Social and Psychological Interventions (CONSORT-SPI) (Montgomery et al., 2018) guidelines and CONSORT extension for the reporting of non-inferiority trials (Piaggio et al., 2012). The trial has been registered on the Australian New Zealand Clinical Trials Registry (ANZCTRN2619001602112). Refer to Appendix I for more details.

The study will commence immediately following ethics approval and recruitment of participants will continue for ~2 years. The overall duration of the study will be 3 years to allow for those in the wait list control condition to complete the intervention and the follow up assessment, and for data analysis and dissemination of results. To test the efficacy of the intervention, the study will test the following hypotheses:

ACT-Adjust intervention: Participants in the active treatment regardless of delivery (FtF vs. VC) will demonstrate increased psychological flexibility and decreased psychological distress following the intervention, compared to those in the control group (waitlist).eHealth: There will be no differences in primary and secondary outcomes between participants who receive the ACT-Adjust intervention by FtF compared to those who receive it via VC.Sustained treatment effects: Participants in the active treatment condition, ACT-Adjust (VC and FtF), will maintain their gains three months post intervention.

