### Treatment Conditions

All participants will receive their intervention in conjunction with constrained usual care (Freedland et al., 2011). Usual care may involve prescribed components of multidisciplinary interventions (e.g., social work, physiotherapy, occupational therapy, case management, speech therapy, diversional therapy, and/or vocational assistance) except for clinical psychology, as well as regular medical reviews by a rehabilitation physician and/or general practitioner. Participants who persistently report extremely high levels of psychological distress (DASS-21 subscales in the extremely severe range, as measured at the beginning of each session) or express suicidal intent during therapy, will be removed from the study and offered immediate psychological treatment. In addition, the treating clinician will assess participants' ability to attend to the session material whether from cognitive impairment or fatigue and make necessary treatment adjustments with regard to rest breaks and/or rescheduling sessions.

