### Data Analysis

Data will be entered into SPSS statistics software (IBM Corp, 2019), reviewed for missing data and then screened for normality on all outcome measures and for each treatment group. Prior to the main analysis, between groups comparisons will be undertaken to test for equivalency of the groups using chi-square and *t*-tests. Where participants withdraw or are not contactable for the follow up assessment, the last recorded measures will be carried forward to remaining assessment points for data analysis. Primary analysis will be implemented on an Intention-to-Treat basis, using hierarchical linear mixed models to study the differential effects of each treatment condition. For the post-treatment analyses between the three treatment conditions, analysis will focus on linear time effects, treatment conditions and interactions. Cohen's effect size will be calculated for all analyses. Analyses will focus on the estimated mean differences relative to pre-treatment levels on primary and secondary outcome measures (see Table 3). For the longer-term treatment effects, the non-inferiority of the face-to-face and video consulting will be assessed at the 3-month follow-up.

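### Carrying last scores forward into the 3-month face-to-face versus video comparison can inflate false non-inferiority claims; the planned mixed model should use observed scores instead

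*Protocol article*

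**What the plan says.** The relevant rules stand together in the Data Analysis section of the protocol article.

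- Missing scores: for people who leave the trial or cannot be reached later, "the last recorded measures will be carried forward to remaining assessment points for data analysis".
- Analysis set: "Primary analysis will be implemented on an Intention-to-Treat basis". The model named for it is a linear mixed model comparing the three conditions.
- Mode comparison: "the non-inferiority of the face-to-face and video consulting will be assessed at the 3-month follow-up". This sentence names no analysis set and no margin. The hypothesis in the Overview of Study Design is worded as "There will be no differences in primary and secondary outcomes between participants" in the two modes.

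Three other sections matter. Treatment Conditions says that participants with persistent extreme distress or suicidal intent "will be removed from the study and offered immediate psychological treatment", which is a planned source of missing outcomes. Session Measures has the DASS-21 and AAQ-ABI taken before each session as well, but Data Analysis does not say whether such a score can be the one carried. Randomization gives 16 FtF, 16 VC and 24 wait-list participants, with the wait list later re-randomised 1:1. The mode comparison is therefore 16 v 16 or, if the re-randomised participants are pooled, 28 v 28. The article does not say which.

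**The concern.** Carry-forward does different things to the two questions. Against the wait list, giving dropouts an early score usually dilutes the treatment effect, which is cautious. In a non-inferiority comparison, dilution works toward the conclusion the trial hopes for. Someone who leaves early in either mode keeps a score from before the modes had much time to diverge. The more such scores there are, the smaller a real VC deficit looks.

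The 3-month time point adds a second difficulty. The section on ACT-Adjust 2.0 says that treatment gains were not sustained in the earlier trial. A post-treatment score carried to 3 months assumes no relapse, so it would hide a VC deficit that appears only after therapy ends.

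At stake is a claim that video delivery is as good as face-to-face when it is worse by the full margin.

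**Working it through.** **The plan's own figure.** The article has no non-inferiority sample size, margin or dropout rate to reproduce. Its one figure, N = 56, is for an interaction test (partial η² = 0.17, power 0.80). With f² = 0.17/0.83 = 0.205 and an assumed alpha of 0.05, a three-group F test needs 51, and 56 gives power 0.85. Rounding 51 up to whole blocks of seven gives 56, though the article does not say this was done. The gap does not bear on this point.

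**Inputs.** From the article: 16 per arm, or 28 if pooled. Assumed: margin M = 0.5 SD (others below); one-sided alpha 0.025; dropout dF and dV of 10-30%; FtF gain G = 0.9 SD (close to 2f = 2 × 0.453 = 0.91); correlation of baseline with outcome 0.5. The true VC deficit is set equal to M, so every non-inferiority claim is false.

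**Direction.** If baseline is carried, the mean gain is G(1 − dF) in FtF and (G − M)(1 − dV) in VC. The expected difference is

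M(1 − dV) + G(dV − dF).

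- Equal dropout d: the deficit becomes M(1 − d), so 0.50 SD becomes 0.45, 0.40 and 0.35 SD at 10, 20 and 30%.
- FtF 30%, VC 10%: 0.45 − 0.18 = 0.27 SD.
- FtF 10%, VC 30%: 0.35 + 0.18 = 0.53 SD, so the bias reverses.
- The modes are pulled together only if dV − dF < dV·M/G. In the reversed case 0.20 exceeds 0.30 × 0.5/0.9 = 0.167.
- If the carried score already holds 80% of each arm's gain and dropout is equal, the deficit is M(1 − 0.2d): 0.49, 0.48 and 0.47 SD.

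**Size by formula (equal dropout q, baseline carried).** False-claim rate = Φ(Mq/SE − 1.96), with SE = √[(2/n)(1 − ρ²)].

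- n = 16, q = 0.2, ρ = 0: SE = 0.354; Φ(0.283 − 1.96) = 0.047. With ρ = 0.5: SE = 0.306; Φ(0.327 − 1.96) = 0.051.
- n = 28, q = 0.2, ρ = 0: SE = 0.267; Φ(0.374 − 1.96) = 0.056. With ρ = 0.5: SE = 0.231; Φ(0.432 − 1.96) = 0.063.

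Over margins of 0.4-0.6 SD, equal dropout of 10-30% and ρ of 0-0.5, the formula runs from 3.2% to 11.9%.

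**Size by simulation** (ANCOVA on baseline, ρ = 0.5, dropout at random, 15,000 runs per scenario, M = 0.5 SD):

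| Dropout FtF / VC | Score carried | 16 per arm | 28 per arm |
|---|---|---|---|
| 10% / 10% | baseline | 0.037 | 0.039 |
| 20% / 20% | baseline | 0.052 | 0.064 |
| 30% / 30% | baseline | 0.076 | 0.099 |
| 30% / 10% | baseline | 0.11 | 0.16 |
| 10% / 30% | baseline | 0.017-0.019 (both sizes) | 0.017-0.019 (both sizes) |
| 10-30%, range over scenarios | holds 80% of gain | 0.023-0.034 | 0.029-0.035 |
| 10-30%, range over scenarios | none (observed scores only) | 0.022-0.028 (both sizes) | 0.022-0.028 (both sizes) |

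The margin changes the picture. At 0.8 SD with 28 per arm, equal dropout of 10, 20 and 30% gives 0.055, 0.108 and 0.200. With 10% FtF and 30% VC dropout, the rate stays inflated at 0.8 SD (0.039-0.045) but falls to 0.013-0.014 at 0.4 SD.

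**The case against.** Three stronger readings are tempting, and the article supports none of them.

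First, a reader might infer that non-inferiority rests on intention-to-treat alone and that the lack of a per-protocol set is the error. The article is condensed, and supporting analysis sets are commonly left to the full protocol or analysis plan. Calling the primary analysis intention-to-treat does not exclude others, and its use for the mode comparison is itself an inference. Nor does citing the "CONSORT extension for the reporting of non-inferiority trials" show which analysis sets the trial has. What remains is the carry-forward rule, which is written down for data analysis in general and extends to the remaining assessment points.

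Second, a reader might infer that carry-forward always draws the two modes together. It does not: clearly higher VC dropout can push them apart, as shown above.

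Third, a reader might infer that every carried score is early and neutral. Someone who misses only the 3-month visit carries a post-treatment score, which already contains any mode difference present then. If session scores count, the last record may be late in therapy. People removed for extreme distress carry poor scores that count against their own arm. The article also says nothing about participants switching mode, so that cannot be counted as a source of dilution.

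These objections limit the size and direction of the bias. They do not defend the rule: a bias whose sign depends on an unknown dropout pattern is a poor thing to fix in advance. It is also unnecessary, because the planned mixed model can use incomplete records.

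**Conclusion.** The point holds in conditional form. Carry-forward is fixed in the plan, reaches the 3-month FtF versus VC assessment, and is a poor choice for it. With similar dropout in both arms and baseline carried, the one-sided false non-inferiority rate at an assumed 0.5 SD margin is about 4-8% (16 per arm) or 4-10% (28 per arm) instead of 2.5%. With clearly more dropout in FtF it reaches 11-16%. If late scores are carried it stays near nominal, at no more than about 3.5%. With clearly more dropout in VC it can fall below nominal.

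The direction follows from the algebra. The size rests on assumed margin, dropout, gain and correlation, none of which the article states for this comparison. The return to about 2.5% without carry-forward assumes ignorable dropout, which removal for distress may violate. This is a worthwhile low-cost improvement; it does not show that the trial's conclusion will be wrong.

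**What to change.** 1. Remove carry-forward. Fit the planned mixed model to all observed scores of all randomised participants, for the wait-list comparison and the mode comparison alike, and state that intention-to-treat applies to both.
2. For VC versus FtF, add a supportive analysis of participants treated in their allocated mode with an observed 3-month score. Define the required sessions in advance. A cut-off before Session 9 would leave out the relapse-prevention session added to sustain gains, so the choice needs a reason. This set must not decide the question by itself: it drops people removed for distress, which could favour VC, and it is not fully protected by randomisation.
3. Add a sensitivity analysis that penalises missing VC outcomes, for example by imputing them progressively worse up to the margin.
4. Claim non-inferiority only if these conclusions agree.

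The data are already to be collected, so the direct cost is a little analysis work. The real cost is that a claim becomes somewhat harder to reach. Power is already modest: with no true difference, no dropout, no baseline adjustment and a 0.5 SD margin, it is 0.29 at 16 per arm and 0.46 at 28 per arm, and 63 per arm would be needed for 80%. An inconclusive result becomes more likely, and the report should be ready to say so.

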### Sample Size and Power Calculations

Based on a previous pilot RCT of the ACT-Adjust program (Whiting et al., 2020), sample size calculations on the primary outcome measure (AAQ-ABI) indicate a total sample size of 56 (ES Partial η^2^ = 0.17, Power = 0.80), is required to establish a significant interaction effect from pre to post intervention. A previous RCT for a psychological intervention conducted at the Liverpool Hospital, Brain Injury Rehabilitation Unit screened *n* = 90 participants with *n* = 17 meeting study criteria and agreeing to participate in the trial (Simpson et al., 2011). Using this ratio, it is anticipated ~*n* = 297 participants will need to be screened to recruit the required sample for the current trial.

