### Blinding

Psychologists conducting baseline assessments (Time 1) will be blinded to participant treatment allocation, as participants will be randomized after the baseline assessment (Time 1). Blinding of the treating psychologists providing the intervention is not possible, however an independent assessor will be used to complete the post-treatment (Time 2) and 3-month follow-up assessments (Time 3) and will be blinded to the condition. The success of blinding will be assessed by having the independent assessor (i) indicate which condition they think the participant was randomized to (FtF, WL or VC) and (ii) indicate if the participant disclosed their treatment condition. Data analysis will be undertaken by a statistician, from the Ingham Institute for Applied Medical Research but not directly associated with the individual research group, who will be blinded to the treatment conditions. It is not anticipated unblinding will be required for the independent assessor or statistician and therefore is not permissible in this study.

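### The named model estimates a difference in change scores; adjusting for the baseline score already collected would be more precise at no cost, and the baseline significance tests should become a descriptive table.

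*Protocol article*

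**What the plan says.** All of the analysis text is in the Data Analysis section of the protocol article. The primary analysis is by intention to treat, "using hierarchical linear mixed models to study the differential effects of each treatment condition". For the post-treatment comparison of the three conditions, "analysis will focus on linear time effects, treatment conditions and interactions". The reported quantity is then given: "Analyses will focus on the estimated mean differences relative to pre-treatment levels on primary and secondary outcome measures". Before this, "between groups comparisons will be undertaken to test for equivalency of the groups using chi-square and *t*-tests". No consequence of those tests for the model is stated.

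The Sample Size and Power Calculations section powers the same quantity. A total of 56 ("ES Partial η^2^ = 0.17, Power = 0.80") "is required to establish a significant interaction effect from pre to post intervention", on the AAQ-ABI. The Randomization section allots 16 to face-to-face, 24 to waitlist and 16 to video. The Blinding section says that randomisation follows the baseline assessment.

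**The concern.** The waitlist arm is re-randomised after Time 2, so the three-arm comparison has two assessments, baseline and Time 2. If baseline is one of the outcomes and each arm has its own baseline mean, the treatment-by-time term is exactly the difference between arms in mean change. That subtracts the whole baseline score, although only part of it predicts follow-up when r is below 1. The rest of the baseline variation goes into the contrast as noise.

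This matters most for video against face-to-face, with 16 per arm at the first randomisation. The article expects to screen about 297 people to recruit 56, so precision that needs no recruitment is worth having. The baseline score precedes randomisation and is therefore a valid covariate.

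The equivalency tests are a separate matter. After randomisation any baseline difference is due to chance, so they test a null that is known to be true. With arms this small, a non-significant result does not show equivalence.

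**Working it through.** **Inputs.** From the article: N = 56; arms 16/24/16; partial eta squared 0.17; power 0.80. Assumed, because not stated: alpha 0.05; pre-post correlation r from 0.3 to 0.8; equal variance at baseline and follow-up.

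**The stated 56.** f² = 0.17/0.83 = 0.2048. A three-group F test (noncentral F) needs N = 51 with noncentrality f²N, or 53 with f²(N − 3). Rounding either up to whole blocks of seven gives 56. That explains the figure without proving that it was derived so. It has no bearing on this point.

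**Named model against change score.** In one simulated trial of 56, a mixed model with group, time and their interaction gave an estimate of 0.946 with standard error 0.252. A direct comparison of change scores gave the same two figures. Baseline adjustment gave a standard error of 0.242.

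**Variance ratio.** With common SD s:
- change score: residual variance 2s²(1 − r)
- baseline-adjusted: residual variance s²(1 − r²)
- ratio: (1 − r²)/[2(1 − r)] = (1 + r)/2

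| r | Ratio | Adjusted N matching 56 on change | Adjusted power if change has 80% (three-group F) |
|---|---|---|---|
| 0.3 | 0.65 | 37 | 94% |
| 0.5 | 0.75 | 42 | 90% |
| 0.7 | 0.85 | 48 | 86% |
| 0.8 | 0.90 | 51 | 84% |

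Simulation at 16/24/16 gave ratios of 0.655, 0.753 and 0.861 for r = 0.3, 0.5 and 0.7.

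**Half-width, video against face-to-face, 16 v 16.** At r = 0.5 the change-score SD equals s.
- change: t(30) × √(2/16) = 2.042 × 0.354 = 0.72
- adjusted: t(29) × √(0.75 × 2/16) = 2.045 × 0.306 = 0.63

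In units of s, the fall is from 0.85 to 0.69 at r = 0.3, and from 0.56 to 0.52 at r = 0.7.

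**Chance imbalance.** The standard error of a baseline difference at 16 v 16 is √(2/16) = 0.35 SD. An imbalance of that size shifts the change contrast by (1 − r) × 0.35, which is 0.25, 0.18 and 0.11 SD for r = 0.3, 0.5 and 0.7. This is the same noise seen within a single trial, not a further bias.

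**Effect of the DASS-21 entry cut-offs.** Eligibility Criteria sets cut-offs on the DASS-21, and Table 3 places the eligibility screen and the DASS-21 both at T1. As an illustration, take bivariate normal scores with unit variances, unselected correlation 0.5, and entry only above the baseline mean. Baseline variance becomes 1 − 2/π = 0.363. The slope stays at 0.5, so the adjusted residual variance is 0.75. The change variance is 0.75 + (1 − 0.5)² × 0.363 = 0.841. The ratio is 0.75/0.841 = 0.89, not 0.75. The same calculation gives 0.84 for an unselected correlation of 0.3 and 0.94 for 0.7. The true degree of selection is unknown.

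**Equivalency tests.** At 16 v 16, a two-sided t-test at 0.05 has about 28% power to detect an imbalance of 0.5 SD.

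**The case against.** The strongest reply is that the article only says what the analysis will focus on, that a mixed model can carry a baseline covariate or a common baseline mean, and that such detail often sits in an analysis plan that is not shown. In part this stands. A reader might infer that the plan rejects baseline adjustment, or uses the equivalency tests in its place. The text says neither: it does not link those tests to adjustment, and the tests themselves cost no precision. What does not stand is the idea that the text is neutral. It names a treatment-condition term next to time and the interaction, reports differences from the pre-treatment level, and powers the pre-to-post interaction. A common-baseline model does not fit the named treatment term well.

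Three more limits are fair:
- The change-score contrast is unbiased under randomisation, and regression to the mean acts equally on the arms in expectation. The planned analysis is not invalid.
- It is tempting to say that t-tests cannot serve three arms. Pairwise t-tests can, so that is no fault.
- One might quote the gain at 28 v 28, by adding the 24 waitlist participants re-randomised 1:1. Data Analysis does not state such pooling, so the figure here stays at 16 v 16.

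**Conclusion.** The point holds as one of efficiency, not of error. As written, the model gives the difference in change scores, and baseline adjustment would cut the variance of the treatment contrasts by 35%, 25%, 15% or 10% for r = 0.3, 0.5, 0.7 or 0.8. These figures rest on an assumed r and on equal variances. They suit the AAQ-ABI, which is not an entry criterion and is the outcome used for the sample size. On the DASS-21 the gain may be clearly smaller; in the illustration with an unselected correlation of 0.5 it is about 11%. The equivalency tests are uninformative after randomisation, whatever model is chosen.

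**What to change.** State that post-baseline scores are modelled with the baseline score of the same scale as covariate, and that treatment effects are read from treatment-by-time contrasts. A longitudinal model with baseline means constrained to be equal across arms is an acceptable alternative. Remove the chi-square and t-tests of equivalency and show baseline characteristics by arm descriptively. The cost is a few sentences in the analysis plan: the baseline scores are already collected before randomisation, and sample size and visits do not change.

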### Eligibility Criteria

Inclusion criteria will comprise: (i) having sustained a severe TBI (post-traumatic amnesia =>7 days) after 18 years of age; (ii) being between 18 and 65 years old; (iii) <5 years post-injury; (iv) having sufficient cognitive-linguistic capacity to complete self-report measures and participate in the program; and (v) reporting a clinically significant level of psychological distress (Depression >13, Anxiety >9, and Stress >18; Depression Anxiety Stress Scales 21-item; DASS-21) (Lovibond and Lovibond, 1995). Exclusion criteria are: (i) having a severe psychiatric illness, including psychotic disorder or substance addiction as determined by the medical file, self-report or consultation with the rehabilitation team; (ii) currently receiving a psychological intervention; and (iii) living >1-h travel distance from a psychologist able to deliver the intervention, to ensure access to a psychologist regardless of whether the therapy is delivered FtF or by VC.

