Each participant enrolled in the trial will receive a Therapy Kit comprising a hardcopy of the ACT-Adjust 2.0 Client Workbook and individually wrapped materials for Session 2 (Chinese finger trap), Session 5 (packet of sultanas), and Session 6 (values card pack). All participants will complete the ACT-Adjust 2.0 program (Table 1), which is comprised of 9 × 1.5 h sessions. The week prior to commencing the program (and before randomization occurs), participants will meet with the treating psychologist in person to complete Baseline assessments. Sessions 1–7 will occur on a weekly basis, and a 2-week break will be placed between Sessions 7 and 8, and a 4-week break between Sessions 8 and 9. If required, sessions may be rescheduled by arrangement between the participant and treating psychologist, and will be rescheduled as soon after the original session as is feasible. Following the completion of Session 9, participants will meet with an independent blinded assessor to complete the Time 2 assessment measures (within 1 week of treatment completions). Three months after completing Session 9, participants will meet again with an independent blinded assessor to complete Time 3 assessment measures.

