#### Primary Outcome Measures

*Psychological distress*—*Depression Anxiety Stress Scales* −*21 (DASS-21)* (Lovibond and Lovibond, 1995) is a 21-item questionnaire which assesses the constructs of depression, anxiety and stress over a seven-day period. Clinically significant levels of distress on the DASS-21 (87th percentile and above) are defined by the following scores on each subscale; (i) Depression >13, (ii) Anxiety >9, and (iii) Stress >18. The DASS-21 is commonly used in clinical practice within Australia and includes the broader psychological component of stress. The existing factor structure has been replicated in samples with a moderate to severe TBI and internal consistency of the subscales was very good (Cronbach's α > 0.80) (Randall et al., 2017).

*Psychological flexibility*—Acceptance and Action Questionnaire—Acquired Brain Injury (AAQ-ABI) (Whiting et al., 2015) is a nine-item self-report measure scored on a five-point Likert scale with a range of 0–36, with higher scores indicating greater psychological flexibility. Items assess psychological flexibility around the thoughts, feelings and behaviors that may arise after incurring a brain injury, e.g., Item three, “*I stop doing things when I feel scared about my brain injury*.” The measure has sound psychometric properties (e.g., Cronbach's α = 0.89) (Whiting et al., 2015).

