			**Study period**								
			**Enrolment**	**Allocation**	**Post-allocation**						
					**Intervention**				**Evaluation**		
Time Points			T1	T1a	T1b	Weeks 1–7	Week 9	Week 13	T2	T3	T4
					VC training	Session 1–7	Session 8	Session 9			
Enrolment		Eligibility screen	X								
		Informed consent	X								
		Randomization		X							
Interventions		ACT-Adjust FtF									
		ACT-Adjust VC			X						
		Wait list Control									
Assessments	Baseline measures	Demographic data	X								
		RBANS	X								
	Primary Outcome measures	DASS-21	X			X^2^	X^2^	X^2^	X	X	X
		AAQ-ABI	X			X^2^	X^2^	X^2^	X	X	X
	Secondary Outcome measures	QOLIBRI	X						X	X	X
		SLP	X						X	X	X
		ELS	X						X	X	X
		SWLS	X						X	X	X
	Other measures	HTRS^1^				X^2, 3^	X^2, 3^	X^2, 3^			
		SRS V.3				X^3^	X^3^	X^3^			
		VCSE-Client				X^3^	X^3^	X^3^			
		VCSE-Therapist				X^3^	X^3^	X^3^			

1 *Items 1-2 administered at end of the session and Item 3 at the beginning of the following of session*;

2 *Measure administered at the beginning of the treatment session*;

3 *Measure administered at the conclusion of the treatment session. AAQ-ABI, acceptance and action questionnaire-acquired brain injury; DASS-21, depression anxiety stress scales −21; ELS, enhanced living scale; HTRS, home task rating scale; QOLIBRI, quality of life after brain injury; RBANS, repeatable battery for the assessment of neuropsychological status; SWSL, satisfaction with life scale; SRS V.3, session rating scale version 3; VCSE, video consulting session evaluation*.

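### A 3-month DASS-21 gain measured from the T1 entry score, with no untreated arm left, includes regression to the mean and can make a faded effect look maintained

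*Protocol article*

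**What the plan says.** Under Eligibility Criteria, entry requires "reporting a clinically significant level of psychological distress (Depression >13, Anxiety >9, and Stress >18; Depression Anxiety Stress Scales 21-item; DASS-21". Primary Outcome Measures describes how extreme these cut-offs are: "Clinically significant levels of distress on the DASS-21 (87th percentile and above", without naming the reference population.

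Table 3 places the row "Eligibility screen" and the only DASS-21 before allocation in the same column, T1. The section on ACT-Adjust 2.0 describes one baseline visit: "The week prior to commencing the program (and before randomization occurs), participants will meet with the treating psychologist in person to complete Baseline assessments". No separate screening DASS-21 is scheduled.

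Data Analysis sets the reference for results: "Analyses will focus on the estimated mean differences relative to pre-treatment levels on primary and secondary outcome measures". It also calls for Cohen's effect size for every analysis.

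Hypothesis 3 (Overview of Study Design and Research Hypotheses) is that the two active arms "will maintain their gains three months post intervention". It names no comparator. The timing is: "Three months after completing Session 9, participants will meet again with an independent blinded assessor to complete Time 3 assessment measures". By then the wait list has been re-randomised to active treatment (Randomization; Wait List Control Condition). The only 3-month analysis described is the comparison of the two delivery modes, both treated. Appendix I lists change in DASS-21 at 3 months within the primary outcome.

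**The concern.** People admitted because a noisy score was high will on average score lower at the next measurement, treated or not. If the admitting score is also the starting point, part of any later fall is this artefact.

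Up to T2 the wait list shows the same fall, so the randomised difference removes it. At T3 nothing removes it from a change computed within the treated arms. Hypothesis 3 concerns exactly that group at that time, and the stated reference is the pre-treatment level.

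Durability matters here. The description of ACT-Adjust 2.0 says that the earlier programme's gains were not sustained and that Session 9 was added for that reason. A reader of the results will look to the 3-month DASS-21 change for the answer.

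**Working it through.** **Inputs from the article.** Face-to-face 16 + video 16 = 32 treated; wait list 24. T2 falls at about 13 weeks; T3 is three months after Session 9. The article gives no figure of its own on this point: the sample size of 56 was derived for the AAQ-ABI and enters only through the arm sizes.

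**Assumptions.** The article gives no test-retest correlation r over these intervals, so r = 0.7 to 0.9 is assumed. How selective the cut-offs are among people actually screened is also unknown, so three cases are shown: cut-off at the 30th percentile, the median and the 87th percentile of the screened pool. Scores are normal, with a stable level plus independent occasion error. One cut-off is modelled, for simplicity.

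**Step 1: expected fall with no treatment.** With a share q above the cut-off z, the mean excess at T1 is φ(z)/q, and the expected fall is (1 − r) × φ(z)/q.

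- 87th percentile: q = 0.13, excess 1.63 SD; at r = 0.7 the fall is 0.3 × 1.63 = 0.49 SD.
- Median: q = 0.50, excess 0.80 SD; fall 0.3 × 0.80 = 0.24 SD.
- 30th percentile: q = 0.70, excess 0.50 SD; fall 0.3 × 0.50 = 0.15 SD.

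The table adds the simulated chance that 32 treated participants show a significant T1-to-T3 improvement when treatment does nothing (two-sided 5% test, so nominally 2.5% in that direction).

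| Cut-off in screened pool | r = 0.7 | r = 0.8 | r = 0.9 |
|---|---|---|---|
| 30th percentile | 0.15 SD, 18% | 0.10 SD, 15% | 0.05 SD, 8% |
| Median | 0.24 SD, 44% | 0.16 SD, 29% | 0.08 SD, 17% |
| 87th percentile | 0.49 SD, 96% | 0.33 SD, 86% | 0.16 SD, 53% |

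Requiring all three cut-offs, as the criterion is written, gives a similar range. At r = 0.7, subscale correlation 0.6 and 13% to 50% of the pool above each cut-off, the fall per subscale is 0.14 to 0.27 SD if occasion noise is independent across subscales and 0.30 to 0.55 SD if it is shared.

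**Step 2: the randomised comparison.** In the same simulations the treated against wait-list contrast at T2 rejects in 4.3% to 5.7% of runs with no effect. It is sound.

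**Step 3: an effect that fades.** Let the T2 effect be 0.6 SD and the T3 effect zero. With regression of 0.24 SD (median cut-off, r = 0.7), the expected changes are:

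- treated, T1 to T2: 0.60 + 0.24 = 0.84 SD fall
- treated, T1 to T3: 0 + 0.24 = 0.24 SD fall
- wait list, T1 to T2: 0.24 SD fall
- treated T1-to-T3 fall net of wait list: 0.24 − 0.24 = 0

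At r = 0.7 across the three cut-offs, a positive T2 contrast together with a significant T1-to-T3 fall occurs in 18% to 83% of simulated trials, although nothing is left of the effect at T3. Replacing the uncontrolled fall by the netted gain cuts this to 2% to 3%.

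**Step 4: price of netting.** With equal variances of change and complete data, the ratio of standard errors is √(1/32 + 1/24) / √(1/32) = √(1 + 32/24) = 1.53.

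**The case against.** **The article never states a within-arm T1-to-T3 test.** True. The quoted sentence comes soon after the text on the three-arm analysis and can be read as between-arm differences in change, which are unaffected. How Hypothesis 3 is tested may be set out in a fuller document. The point is therefore limited to what this text fixes: a reference level that does not suit a treated-only claim on a variable used for selection.

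**A reader might infer that maintained gains would be declared even if ACT-Adjust did nothing.** The documents do not support that. To maintain a gain presupposes one, and Hypothesis 1 tests for it against the wait list. With no effect at all, a positive Hypothesis 1 plus a significant T1-to-T3 fall occurs in only 1% to 3% of simulated trials. The danger lies in a real T2 effect that fades, and in an overstated 3-month effect size.

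**The entry score may not be the T1 score.** No sentence says that it is; this is read from Table 3. Recruitment Process mentions a screening consent form, which leaves room for a separate screen. If a separate DASS-21 was used and errors are independent, the spurious gain is about zero.

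**A T2-to-T3 comparison would be enough.** It would show a loss, so it belongs in the assessment. Alone it is not enough: once scores have regressed by T2, no further change looks like maintenance, and carrying T2 values forward for later dropouts adds to that appearance.

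**The 87th percentile probably describes a reference population.** Also fair. Referred patients are likely to be more distressed, so the lower rows of selectivity may be closer to the truth.

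**Conclusion.** The point holds for DASS-21 and for Hypothesis 3 only. On the reading of Table 3 that the entry score is the T1 score, a T3 minus T1 change within the treated arms mixes any lasting effect with regression to the mean, and no arm at T3 can separate them. The inflation is about 0.05 to 0.5 SD for r = 0.7 to 0.9, depending on how selective the cut-offs are in the screened pool. Both r and the selectivity are assumptions.

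Hypothesis 1 at T2 and the comparison of delivery modes at T3 are not biased, because regression is equal across arms in expectation. The AAQ-ABI is not an entry variable and is touched only through its correlation with DASS-21. Because the correction needs only scheduled data, it is worth making despite the uncertain size.

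**What to change.** In Data Analysis, for DASS-21, state that:

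1. Hypothesis 3 is judged only after a positive ACT-Adjust against wait-list contrast at T2.
2. It is then judged on two estimates from the same mixed model: the T2-to-T3 change in the treated arms, and their T1-to-T3 gain net of the wait-list T1-to-T2 change. Visits should be fitted as categories so that both contrasts can be estimated.
3. The uncontrolled T3 minus T1 change and its Cohen's effect size are not presented as a maintained treatment gain.

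It would also help to say in words whether the entry DASS-21 is the T1 score.

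**Cost.** No new data. The standard error of the netted gain is about 1.5 times that of the uncontrolled one. Netting also assumes negligible natural change after T2, because the wait-list interval of 13 weeks is shorter than T1 to T3.

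The Session 1 DASS-21 (Table 3, note 2: "Measure administered at the beginning of the treatment session") may look like a ready second baseline. I would not use it. It is taken after allocation, about a week after T1 on a seven-day scale, so some shared error may remain, and it is given by the unblinded treating psychologist.
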